#### **7.4.3. Management of Symptoms during Infusion**

Mild transient symptoms have been observed with LAK and TIL cell infusions and, with infusions of antigen-specific T cell clones (protocol 1017). The management of these symptoms is outlined below.

- a. Fever, chills and temperature elevations  $> 101^{\circ}\text{F}$  will be managed with acetaminophen 650 mg p.o. q 4-6 hrs. All subjects that develop fever or chills will have a blood culture drawn.
- b. Headaches may be managed with acetaminophen following a neurologic examination.
- c. Nausea, vomiting will be treated with a non-steroidal anti-emetic of choice.
- d. Hypotension will initially be managed by intravenous fluid administration and further measures as dictated by standard medical practice.
- e. Hypoxemia will initially be managed with supplemental oxygen and further measures as dictated by standard medical practice.

#### **7.4.4 Potential Toxicities Warranting Ablation of Adoptively Transferred Cytotoxic T Cell Clones**

The following will be considered Dose-Limiting Toxicities (DLT):

- a. Ophthalmologic: Patients receiving T cells targeting tyrosinase, MART-1 or gp100 will undergo a pre-therapy ophthalmologic exam and particular attention in the post-infusion monitoring period be given to ocular toxicity. The presence of retinitis or choroiditis as determined by ophthalmologic exam will be coded as a grade 3 toxicity and will warrant administration of steroids to ablate transferred T cells. If symptoms of visual field impairment arise, a formal visual fields examination will be conducted to determine if such a visual field defect exists. Any defect in the visual field will warrant T cell ablation.
- b. Grade 2 or greater allergic reaction of: asymptomatic bronchospasm, or generalized urticaria
- c. Grade 3 or greater toxicity (NCI Common Toxicity Criteria (66)) occurring in any other organ system following administration of antigen-specific cytotoxic

T cells and not attributable to underlying metastatic melanoma or other identifiable cause and excepting :

- i. Fever > 40C for less than 24 hours
- ii. WBC < 1000 for less than 4 weeks
- iii. Platelets < 50,000 for less than 4 weeks
- iv. ANC < 500 for less than 4 weeks
- v. Lymphocytes < 500 for less than 4 weeks

#### **7.4.5 Treatment with Corticosteroids**

- a. Patients will receive corticosteroids if treatment-related toxicity warranting ablation of T cells is observed
- b. All patients will be hospitalized for the first 48 hours for monitoring. The following dose schedule will be used:

|           |                                    |
|-----------|------------------------------------|
| Day 1     | Intravenous Solu-Medrol at 2 mg/kg |
| Day 2     | Intravenous Solu-Medrol at 2 mg/kg |
| Day 3-4   | Prednisone at 30 mg po b.i.d.      |
| Day 5-6   | Prednisone at 15 mg po b.i.d.      |
| Day 7-8   | Prednisone at 10 mg po b.i.d.      |
| Day 9-10  | Prednisone at 10 mg po q.d.        |
| Day 11-12 | Prednisone at 5 mg po q.d.         |

- c. The in vivo frequency of infused CD4+ T cells will be assayed immediately prior to and 48 hours after the start of steroid therapy. If the frequency of infused CD4+ T cells as determined by peptide-tetramer and RT-PCR analysis of a clone-specific CDR3 region of the TCR at this time has not decrease to 25% or less of the T cell frequency prior to infusion, then, high-dose Solu-Medrol at 2 mg/kg will be given for an additional 48 hours before continuing with the tapering dose schedule.

#### **7.4.6 Management of Chronic Toxicity**

Based on animal models of T cell mediated autoimmunity, it is anticipated that if toxicity due to the infused T cells should occur, such events will be acute and, if significant, will result in the timely removal of the patient from the study and administration of steroids and/or discontinuation of the study. However, unforeseen chronic or delayed autoimmune toxicities may not permit a timely intervention. These patients will be treated high-dose steroids to mediate lympholytic and anti-inflammatory effects and any other measures to ameliorate toxicity, including chronic steroid therapy.

### **7.5 CONCOMITANT THERAPY**

- #### **7.5.1**
- Active infections occurring after initiating the study should be treated according to the standard of care.

**7.5.2** The following agents are not allowed while on study: systemic corticosteroids (except as outlined for management of toxicity of non-transduced CTL), immunotherapy (for example, interleukins, interferons, melanoma vaccines, intravenous immunoglobulin, expanded polyclonal TIL or LAK therapy), pentoxifylline, or other investigational agents.

## **7.6 PREMATURE DISCONTINUATION**

Subjects who do not complete the study medication will be considered to have prematurely discontinued the study. The reasons for premature discontinuation (for example, voluntary withdrawal, toxicity, death) must be recorded on the case report form. A subject may re-enter the study after premature discontinuation only by approval of the Principal Investigator. If possible, final study evaluations should be completed at the time of discontinuation. Potential reasons for premature discontinuation include:

**7.6.1** The development of a life-threatening infection.

**7.6.2** Judgment of the principal investigator that the patient is too ill to continue.

**7.6.3** Patient noncompliance with study therapy and/or clinic appointments.

**7.6.4** Pregnancy.

**7.6.5** Voluntary withdrawal; a patient may remove himself/herself from the study at any time without prejudice.

**7.6.6** Significant and rapid progression of melanoma requiring alternative medical or surgical intervention including, but not limited to, the development of CNS metastasis.

**7.6.7** Grade III or IV toxicity judged to be possibly or probably related to study therapy and fulfilling the stopping criteria as described in 7.4.2.

**7.6.8** Termination of the study by the principal investigator, the Institutional Review Office or the Food and Drug Administration.

## **8. SCHEDULE OF EVALUATIONS**

### **Please see Appendix D for Schedule**

#### **8.1 Immunologic Studies.**

Patients receiving T cells will have 40 mls of heparinized blood and a 6ml gray top tube drawn immediately prior to each infusion and 24 hours after each infusion and once weekly for 10 weeks as outlined in appendix D. Samples will be used to evaluate the duration of in vivo persistence, function and trafficking of infused T cell clones. All blood samples will be kept at room temperature and sent to Rm D3-235, FHCRC

#### **8.2 Efficacy Assessment**

This will be applicable only for those patients who presented with measurable disease.

##### **8.2.1 Clinical Response.**

Radiographic imaging and clinical assessment of residual disease will be compared with pre-infusion assessment. A complete response will be defined as total regression of tumor, a partial response as 50% or more regression of the sum of the perpendicular diameters of all measurable disease, a minor response as less than 50% regression. This assessment will be performed at 4 and 8 weeks following the last infusion and then every 3 months until disease progression or intervening therapy.

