### **2.4 Adoptive T Cell Therapy for Metastatic Melanoma Using Antigen-specific T Cells**

#### **2.4.1 Adoptive T Cell Therapy – CD8+ T Cell Clones**

We recently completed a Phase I study to evaluate the safety, in vivo persistence and efficacy of adoptively transferred CD8+ T cell clones targeting the

tumor-associated antigens, MART1/MelanA and gp100 for the treatment of patients with metastatic melanoma (27). Four infusions of autologous T cell clones were administered, the first without IL-2 and subsequent infusions with low-dose IL-2 for 14 days. Forty-three infusions of MART1/MelanA-specific or gp100-specific CD8+ T cell clones were administered to 10 patients. No serious toxicity was observed. We demonstrated that the adoptively transferred T cell clones persisted in vivo in response to low-dose IL-2, preferentially localized to tumor sites and mediated an antigen-specific immune response characterized by the elimination of antigen-positive tumor cells, regression of individual metastases and minor, mixed or stable responses in 8 of 10 patients with refractory, metastatic disease for up to 21 months (27).

In the absence of co-administered IL-2, the median in vivo survival of T cells in this study was about 7 days. When T cell infusions were given with low dose IL-2 (250,000 U/m^2 s.c. twice daily) for 14 days, median T cell survival was extended to > 16 days. Attempts to enhance T cell survival beyond this period by extending IL-2 administration beyond 2 weeks will likely not be feasible due to the induction of counterregulatory mechanisms following prolonged IL-2 administration (36-38). Indeed, in this study, T cell survival began to decline by day 10, before the 14-day course of IL-2 was completed.

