## **5. PATIENT ELIGIBILITY**

### **5.1 Inclusion Criteria**

- 5.1.1** Histopathological documentation of melanoma concurrent with the diagnosis of metastatic disease.
- 5.1.2** Male or female subject, 18 to 75 years of age
- 5.1.3** Expression of HLA-A2 or A3 as determined by FHCRC HLA typing lab.
- 5.1.4** Karnofsky Performance status of at least 80% (Appendix B) and an expected survival of greater than 6 months
- 5.1.5** Bi-dimensionally measurable disease by palpation on clinical exam, or radiographic imaging (X-ray, CT scan).
- 5.1.6** ANC >2,000/ $\mu$ L and platelet count >100,000/ $\mu$ L (at the time of first T cell infusion).

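### Minor response has no minimum shrinkage and no new-lesion rule, and stable and progressive disease are undefined, so measurement error alone can score as a response

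*Protocol*

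**What the plan says.** Protocol section 8.2.1 sets three categories against the pre-infusion assessment, and section 10 repeats them with the same cut-offs:

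- Complete: "A complete response will be defined as total regression of tumor".
- Partial: "50% or more regression of the sum of the perpendicular diameters of all measurable disease".
- Minor: "a minor response as less than 50% regression".

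On timing, section 8.2.1 states: "This assessment will be performed at 4 and 8 weeks following the last infusion". Assessments then follow every three months until progression or another therapy. Neither section gives a minimum decrease for minor response, a rule on new lesions, or a definition of stable or progressive disease.

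Three other places bear on this:

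- Section 5.1.5 requires "Bi-dimensionally measurable disease by palpation on clinical exam, or radiographic imaging".
- Section 7.4.2.2 suspends the study if, on Day 49, measurable lesions have tripled in sum in at least 4 of the first 6 patients. It does not say what is summed for each lesion.
- Section 2.4.1 describes the group's earlier study as showing "minor, mixed or stable responses in 8 of 10 patients with refractory, metastatic disease".

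**The concern.** The category called minor response begins at any decrease above zero, and on a literal reading at zero itself. Repeat measurement of an unchanged tumor gives a smaller total about as often as a larger one, so error alone can fill the category. A small net decrease with a new nodule is not excluded either, although sections 7.3 and 8.2.2 both expect new nodules. With no stable category, an unchanged patient has no other label.

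Antitumor effect is the only secondary objective (section 3.2.1). The study is open-label and nonrandomized with 12 patients, so no control group would show how many minor responses arise by chance. Section 2.4.1 shows that the group has reported minor responses as evidence of activity before.

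**Working it through.** The protocol gives no figure for this category, so there is none to reproduce. The check asks what the written rule does.

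**Inputs.** From the protocol: the three definitions, 12 patients, and assessments at 4 and 8 weeks. Assumed, because the protocol gives none: lesions of 20 mm in each diameter, 1 to 5 lesions, and independent symmetric error on each diameter with SD 3% to 20%, at baseline and at follow-up.

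**1. Unchanged disease, one assessment.** Let B and F be the measured diameter sums at baseline and follow-up. With no true change and symmetric error, F − B is symmetric about zero, so P(F < B) = 0.5 when there are no ties. Simulation gave P(0 < apparent regression < 50%) = 0.498 to 0.502 at every SD and lesion count.

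**2. Rounding to whole millimetres.** Exact ties occur, and P = (1 − P(tie))/2. The tie rate ran from 0.301 (SD 3%, one lesion) to 0.022 (SD 20%, five lesions). The formula gives 0.350 to 0.489; simulation gave 0.348 to 0.491.

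**3. Two follow-up visits.** If shrinkage at either visit counts, a patient escapes only when baseline is the smallest of three exchangeable measurements: 1 − 1/3 = 0.667 (simulated 0.666).

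**4. True growth g.** Take SD 0.10 for the log change from baseline to follow-up (one lesion, 10% error per diameter). Then P(apparent shrinkage) = Φ(−ln(1 + g)/0.10):

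- g = 10%: Φ(−0.953) = 0.170
- g = 20%: Φ(−1.823) = 0.034

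**5. What this means for 12 patients, one assessment each.** P is the binomial chance of three or more apparent minor responses if all 12 share the same rate.

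| Assumed truth | Rate | Expected of 12 | P(3 or more) |
|---|---|---|---|
| No change, no rounding | 0.50 | 6.0 | 0.98 |
| No change, coarsest rounding case | 0.35 | 4.2 | 0.85 |
| 10% growth | 0.17 | 2.0 | 0.33 |
| 20% growth | 0.034 | 0.4 | 0.007 |

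**6. Literal reading.** A regression of 0% is below 50%, so unchanged disease would qualify essentially every time.

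**7. Effect of a floor.** With an illustrative 25% floor on the diameter sum, unchanged disease is called a minor response in 0.0% to 0.2% of assessments at error SD up to 10%, and in at most 7.8% (SD 20%, one lesion). The floor depends on the measure. On the product of the two diameters, with one lesion and 10% error per diameter, the log change has SD 0.10 × √4 = 0.20, and Φ(ln 0.75/0.20) = Φ(−1.44) = 0.075.

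**8. Sum or sum of products.** If every diameter shrinks by the same factor s, the diameter sum scales by s and the area by s². A 50% fall in the sum is therefore a fall in area of 1 − 0.5² = 75%. A 50% fall in area is a fall in the sum of 1 − √0.5 = 29.3%. The two readings would class that patient differently.

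**The case against.** **The zero-change scenario is unlikely.** Section 7.4.2.2 expects progression, with an average time to progression of 2.4 to 4.9 months, and the first assessment comes four weeks after the second infusion. This stands. A reader might infer that half the patients will be scored as minor responders by chance, or that three or more are 98% certain. The documents do not support that as a forecast, because it needs zero true change in all 12 patients. What remains is that the rule gives no protection in the patients whose disease is close to stable.

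**The sum of diameters is a legitimate choice.** This also stands. A reader might infer that the protocol wrongly denies partial response to a 50% area reduction. It sets no area criterion, and bidimensional eligibility is compatible with adding two diameters per lesion. The written rule is a stricter yardstick or loose wording for products. The inference also fails in general: if sixteen 1×1 lesions vanish beside an unchanged 4×4 lesion, area falls from 32 to 16 (50%) while the diameter sum falls from 40 to 8 (80%), which is a partial response.

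**Growing lesions are not ignored.** Correct: they enter a sum taken over all measurable disease, and new measurable lesions can be read as included. The gap is narrower: nothing says that a new lesion rules out a response.

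**No response rate is defined.** Correct. The protocol does not pool minor responses with others and bases no test or decision on them. In section 2.4.1 the group listed stable disease separately, so it probably does not intend the literal reading that includes 0%. That also shows that the current definitions lack a category the group uses.

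**Conclusion.** The point holds as a fault in a stated rule, not as missing detail: both sections define the category, and the definition has no floor, no new-lesion condition and no neighbouring stable or progressive category. For a single assessment of truly unchanged disease with symmetric error, 0.35 to 0.50 would be scored as minor response, depending on rounding. With 10% true growth this is about 17%, and with 20% growth about 3%, given 10% error on the change. Error size, lesion size and lesion number are assumptions; the rate of one half without rounding did not depend on them over the range tried.

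The sum-of-diameters wording is an ambiguity to settle, not a demonstrated error. The consequence is confined to the secondary objective. The sample size, which rests on T cell survival, and the DLT stopping rules are unaffected.

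**What to change.** In sections 8.2.1 and 10, with identical wording:

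1. State whether tumor burden is the sum of the perpendicular diameters or the sum of their products.
2. Give minor response a pre-specified lower bound above measurement error on that measure, with no new lesion. A 25% bound is an illustration only; the protocol contains no such figure, and the same percentage protects less on products than on diameters.
3. Define progressive disease for the response assessment, including how new lesions count, and define stable disease as what remains.
4. Report minor responses separately from complete and partial responses.

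The summed-lesion measure in the Day 49 rule (section 7.4.2.2, repeated in Appendix C) must be reconciled with the choice in item 1, so that the protocol does not carry two unexplained tumor measures.

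The cost is a wording amendment using the same scans and measurements. The drawback is that fewer minor responses will be counted.

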##### **8.2.2 Tumor immunophenotyping**

In the absence of complete regression, immunophenotype analysis of the tumor pre-infusion will be compared with persistent tumor nodules or new tumor nodules post-infusion to evaluate for the outgrowth of antigen-loss tumor variants. New nodules will be sampled when they arise. Persistent disease will be sampled 2 weeks following the last T cell infusion. Immunophenotyping will evaluate the expression of targeted antigen (MART-1) as well as other melanoma antigens (e.g. gp100, tyrosinase) and will be performed by the Immunohistochemistry Laboratory at the University of Washington Medical Center. The level of expression will be scored by the pathologist in 'blinded' samples, as 0-4+ with a score of 0 being no expression, 1+, 25% of cells positive; 2+, 50% of cells, 3+, 75% of cells, 4+ 100% of cells. Antigen loss will be defined as the absence of expression of targeted antigens or a significant decrease in expression (defined as a  $\geq 2$  level decrease in score) in post-infusion sample as compared with the pre-infusion sample.. Persistent expression of non-targeted antigen, e.g. gp100, in the post-infusion tumor sample in the presence of antigen-loss as defined above will be considered evidence of outgrowth of antigen-loss variants as a result of immune targeting. Single cell suspensions of tumor samples will also be stained with anti-Class I and Class II antibody to evaluate HLA allele loss as a possible alternative mechanism of immune evasion.

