### 4. STUDY DESIGN

This will be a single center, phase I, open-label, nonrandomized study in 12 individuals with metastatic melanoma (Stage IV disease). Antigen-specific T cells targeting one of the A2 or A3-restricted epitopes of the melanoma-associated antigens listed in Table 1 (Appendix A ) will be generated in vitro.

Patients will receive T cell infusions according to the following schedule:

[figure not shown]

Protocol 1796.00

Antigen-specific CD8+ T cell clones will be administered at a dose of  $10^{10}$  cells/m^2 for both Infusions #1 and #2. The median survival of transferred antigen-specific CTL clones in the presence of low-dose IL-2 (250,000 U/m^2) is approximately 17 days. By the end of 21 days, the frequency of transferred CTL is < 0.1% of the total CD8+ population. Fludarabine 25 mg / m^2 will be administered intravenously daily for 5 days prior to the second infusion of antigen-specific CD8+ CTL clones which will also be administered in the presence of low-dose IL-2. Four weeks after the second infusion, patients will be re-evaluated clinically and radiographic to determine the response to therapy. Serial blood draws during this time will allow us to determine if fludarabine lymphodepletion contributed to a prolongation of the median T cell survival beyond the expected 17 days seen with low-dose IL-2 alone.

If serious toxicity related to the T cell infusions is observed following infusion of CTL clones, , a regimen of corticosteroids will be given, and no further T cell infusions will be administered to the patient.

Subjects will be carefully monitored at regular intervals for a total of approximately 9 months following the last infusion. Evaluations after this time will be carried out by the referring physician who will be asked to notify us of the patient's progress. Peripheral blood from the patient will also be drawn. Patients receiving T cells will have up to approximately 4 tablespoons of blood drawn immediately prior to each infusion, 24 hours after each infusion, and then at specified intervals for 4 weeks from the last infusion (Appendix D). Samples will be used to evaluate the duration of in vivo persistence, function and trafficking of infused T cell clones. As a secondary objective, the residual measurable disease in these patients will also be followed to assess the therapeutic efficacy, if any, of these infusions. The estimated time to completion of the study is 24 months.

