All clones derived from a given study patient are labeled with the patient's initials followed by the name of the peptide for which they are specific and a number designating that specific clone. Data on cell growth and characteristics for each clone are separately recorded and these records retained. Each recipient has a separate laboratory record book for records on growth and characteristics of the T cell clones derived and grown from that individual. All records with the results of testing performed on the T cell clones are entered into the record book.

When the GMP cell sorting facility becomes available (expected date: July 2003), the following approach may be adopted for the generation of T cell clones.

A dendritic cell-enriched population of adherent PBMCs are harvested following 7-day incubation with GM-CSF and IL-4. They are pulsed with the peptide of interest and co-cultivated CD4 depleted responder T cells in 6-well plates. IL-2 (10 U/mL) is added the following day. After 7 days in culture, the cultures are harvested, washed and re-suspended in staining solution (1% human serum in PBS) containing 50  $\mu$ g/mL of PE-conjugated specific peptide-tetramer and anti-CD8 FITC antibody (Caltag) at a cell concentration of 10^7 cells/mL. After one hour at 4°C, the cells are washed and re-suspended in staining solution for flow cytometry analysis and cell sorting. CD8+ tetramer+ cells are analyzed and sorted under GMP conditions using the high-speed cell sorter at the University of Washington Clinical Research Center facility. They are directly cloned into 96-well plates containing irradiated feeder cells (5x10^4 PBL/well and 10^4 LCL/well) with 30 ng/mL of a CD3 and IL-2 (50 U/mL). Wells positive for clonal growth are selected 10 to 14 days after plating and screened in a microcytotoxicity assay to identify those clones with cytolytic activity for antigen+tumor targets. The use of tetramers is expected to decrease the time from patient enrollment (leukapheresis) to T cell infusion from 2 1/2 months to 6 weeks.

Protocol 1796.00

Table 1. Candidate Target Antigens, HLA restriction and Epitope sequence

| Antigen                  | HLA       | A.A.    | Peptide Sequence |
|--------------------------|-----------|---------|------------------|
| TYROSINASE | A2 | 368-377 | YMDGTMSQV        |
| GP100      | A2 | 154-162 | KTWGQYWQV        |

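### The antigen-loss rule in Protocol 8.2.2 names MART-1 as the target although a clone may target any of seven antigens, and its absence limb sets no baseline

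*Protocol*

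**What the plan says.** Protocol 8.2.2 compares tumour sampled before infusion with persistent or new nodules afterwards. It names what is stained: "Immunophenotyping will evaluate the expression of targeted antigen (MART-1) as well as other melanoma antigens (e.g. gp100, tyrosinase". Samples are scored blinded from 0 (none) through 1+ (25% of cells), 2+ (50%) and 3+ (75%) to 4+ (100%).

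The rule has two limbs joined by an or: "Antigen loss will be defined as the absence of expression of targeted antigens or a significant decrease in expression". The second limb needs a fall of at least 2 levels, and the sentence ends by setting the post-infusion sample against the pre-infusion one. If loss is present and a non-targeted antigen persists, with gp100 as the example, the section concludes that immune targeting drove the outgrowth of antigen-loss variants.

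Elsewhere the target is not fixed. Section 4 describes T cells "targeting one of the A2 or A3-restricted epitopes of the melanoma-associated antigens listed in Table 1". That table, in Appendix A, is headed "Candidate Target Antigens, HLA restriction and Epitope sequence". Section 7.4.4 likewise expects more than one target: "Patients receiving T cells targeting tyrosinase, MART-1 or gp100 will undergo a pre-therapy ophthalmologic exam". On entry, 5.1.3 asks for "Expression of HLA-A2 or A3 as determined by FHCRC HLA typing lab". Neither 5.1 nor 5.2 requires the tumour to express the antigen chosen.

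**The concern.** A rule meant to show that the infused cells removed target-bearing tumour must look at the antigen those cells recognise. The label in 8.2.2 fits only patients given MART-1 clones. For anyone else, a reader following the label scores an antigen that the cells were not directed at, and may treat the real target as the comparator.

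The absence limb raises a second question. The section treats a one-level fall as not significant, yet absence is satisfied by any score of 0 after infusion, with no stated requirement on the score before.

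What is at stake is interpretation. Section 2.5 says a uniform clone population is used so that reasons for success or failure can be defined more clearly, and 8.2.2 turns the score into a causal statement. With 12 patients, and research-only biopsy optional under 7.3, one or two misread cases could change that account.

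**Working it through.** The protocol states no figure for this readout, so there is none to reproduce. The check compares the sections and then enumerates the rule.

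**Step 1. Which antigen is the target?** Table 1 of Appendix A lists seven antigens with their HLA restriction.

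| Antigen | HLA | Role given in 8.2.2 |
|---|---|---|
| MART-1 | A2 | target |
| gp100 | A2 | other antigen; example of non-targeted |
| Tyrosinase | A2 | other antigen |
| MAGE-1 | A3 | not named |
| MAGE-4 | A2 | not named |
| MAGE-10 | A2 | not named |
| NY-ESO-1 | A2 | not named |

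- Not MART-1: 7 − 1 = 6 antigens.
- Outside the three stains named: 7 − 3 = 4 antigens.
- A3-restricted: one, MAGE-1. A patient with A3 but not A2 is eligible under 5.1.3 and can only receive a MAGE-1 clone, so for that patient the MART-1 label cannot be right.

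These are counts of table rows. They do not say how many of the 12 patients would be affected.

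**Step 2. What does the label do?** Take a gp100-directed clone, with MART-1 falling by 2 levels and gp100 persisting. Applied as labelled, MART-1 is lost and gp100 persists as the non-targeted antigen, so the rule concludes immune targeting. Applied by role, gp100 is the target and has not been lost, so the rule concludes nothing. The text permits both.

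**Step 3. What does the absence limb add?** There are 5 × 5 = 25 possible pre/post score pairs.

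- Reading A (absence needs only a post-infusion score of 0): 8 pairs count as loss: 0→0, 1→0, 2→0, 3→0, 3→1, 4→0, 4→1, 4→2.
- Reading B (the pre/post comparison governs both limbs, so absence needs a pre-infusion score above 0): 7 pairs. 0→0 drops out.
- Reference C (a fall of at least 2 levels in every case): 6 pairs. 1→0 also drops out.

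So 0→0 counts only under A, while 1→0 counts under both A and B. Of the four one-level falls (1→0, 2→1, 3→2, 4→3), 1→0 is the only one called loss. The pair counts describe the rule; they are not probabilities.

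**Step 4. Can low baselines occur?** With no expression criterion in 5.1 or 5.2, a tumour scoring 0 or 1+ for the chosen target may enter. The protocol gives no frequency. The section also compares pre-infusion tumour with new nodules, which are different lesions, so a one-level difference need not reflect immune pressure.

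**The case against.** The strongest reply is that the operative sentences speak of roles. Loss is defined for targeted antigens in general, gp100 is only an example, and the list of other stains is open. On that reading the MART-1 parenthetical is a carry-over, gp100 is not the comparator in a gp100-treated patient, and nothing bars staining for a MAGE antigen or NY-ESO-1. This stands in part: wrong scoring is a risk, not a certainty. It does not remove the contradiction, because 8.2.2 still names one target where Section 4, 7.4.4 and Table 1 allow others.

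On the absence limb, the sentence closes with a pre/post comparison and the section opens with one, so a tumour negative both times is naturally read as no loss. That also stands: 0→0 is an ambiguity. It leaves 1→0 untouched. One can argue that complete disappearance differs in kind from a partial fall, and that blinded scoring and the need for a persisting second antigen give some protection. That is a fair reason to keep the limb, but not to pool such cases unmarked with falls of 2 levels or more.

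Finally, the readout is minor. Clinical response (8.2.1) and T cell localization (8.2.3) are separate, and Section 10 does not list immunophenotyping. This is correct and limits the weight of the point.

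**Conclusion.** The point holds in a bounded form. Section 8.2.2 contradicts Section 4, Section 7.4.4 and Table 1 on what the target is: the label fits one of seven permitted antigens and cannot fit a patient with A3 but not A2. The absence limb states no baseline requirement, so 1+ to 0 is a loss on either reading, short of the section's own 2-level threshold, and 0 to 0 is left unclear.

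A reader might infer more, and the documents do not support it:

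- That tumours which never expressed the target are plainly counted as lost. This needs the absence limb to be read apart from the comparison that ends its own sentence.
- That gp100-treated patients will get a reversed result, or MAGE and NY-ESO-1 patients none. The general wording and open list of stains make these risks only.
- That a false-loss rate can be given. The protocol has no data on how far scores vary between samples of an unchanged tumour.
- That non-expressors will enrol. The criteria allow it; no frequency is stated.

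The readout is exploratory, within the secondary antitumour assessment (3.2.1). The primary objectives, safety and persistence, and the sample size are unaffected. It should be corrected because the change is cheap and alters what the readout can conclude.

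**What to change.** In 8.2.2:

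1. Replace the MART-1 label with the antigen targeted by that patient's infused clone, and stain for that antigen on the tissue already sampled.
2. Define the non-targeted comparator as any stained antigen other than that target.
3. State that both limbs require a pre-infusion sample positive for the target.
4. Keep the absence limb, but report 1+ to 0 changes separately from falls of at least 2 levels.

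The cost is a few sentences, plus one matched stain where the target is not already in the panel. Patients negative for the target before infusion become non-evaluable for antigen loss. No change is needed to how each patient's target is chosen. Such a change would alter treatment selection and need pre-treatment tissue from every patient, whereas research-only biopsy is optional (7.3) and 8.2.3 uses a pre-infusion sample only if one is available.
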